## 1. Study objectives

Surgery-induced weight loss is linked to reduction of cancer risk but less is known about the effect of weight loss on cancer subtypes and which patient subgroups benefit the most. Previously, the Swedish Obese Subjects (SOS) study reported an association between surgery-induced weight loss and lower cancer incidence in women, but not men. The aim of this study was to further examine the link between surgery-induced weight loss and long-term cancer outcomes, focusing on patient subgroups defined by previously identified predictors to optimize treatment benefit. Metabolic changes, particularly glycaemic biomarkers and extent of weight loss, have been suggested as key factors linking bariatric surgery to reduced cancer risk.

The analyses presented here were conceived post hoc and were not specified in the original study protocol. While the Swedish Obese Subjects (SOS) study was designed as a prospective, controlled intervention trial, with overall mortality as primary outcome, the present analyses were developed after trial completion to address additional hypotheses regarding surgery-induced weight loss and cancer risk. Therefore, the analyses will be regarded as explorative.

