### 4. Statistical methods

Baseline characteristics will be compared using t-tests (continuous variables) and Fisher's exact test (dichotomous variables). BMI changes will be analyzed with multilevel linear mixed-effects regression models, separately for men and women. The observations will be considered nested within the individuals, and the confidence intervals (CIs) will be calculated taking the repeated measurements into account.

Patients will be analyzed according to their received intervention (i.e. participants will be included in their original study group until any bariatric surgery happens in the control group or there will be a change in, or removal of, the bariatric surgical procedure in the surgery group).

Participants will be followed until the first occurrence of cancer, death, emigration, or end of register-based follow-up (December 31st, 2022). Those who emigrated, died or remained event-free at the end of follow-up will be treated as censored observations in the analyses. In addition, control-group participants who underwent bariatric surgery during follow-up and surgery-group patients who had a procedure restoring normal anatomy will be censored from the analyses at the time point of these operations.

Kaplan-Meier estimates will be used to compare time to first cancer diagnosis or cancer-related death across treatment groups. Cox proportional hazards models will be used to calculate hazard ratios for surgical treatment effects on overall, obesity-related, and female-specific cancers. The proportional-hazards assumption will be evaluated by assessing the interaction between treatment and the logarithm of time. When the assumption is not fulfilled, Cox regression models will be modified to include time-varying effects. Restricted Mean Survival Time (RMST) approach will be used to compare cancer-free time between the surgery and control groups.

To account for baseline differences between the surgery and control groups, analyses will be adjusted for major cancer risk factors defined by the American Cancer Society, age, sagittal diameter, alcohol consumption, and smoking. In addition, serum insulin levels, which have previously been associated with cancer risk in sub-analyses in the SOS study, will be adjusted for. All covariates are selected a priori the actual analyses and will be included in the models regardless of their actual statistical significance.

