To formally test whether baseline insulin modifies the effect of bariatric surgery on cancer risk, an interaction term using the continuous insulin variable will be included in the Cox proportional hazards models. For descriptive purposes, cancer incidence and mortality across subgroups defined by the tertiles of baseline insulin were presented.

The association between weight change and cancer risk will be assessed using the Cox proportional hazard regression model, including one year weight change in the models. These analyses will be restricted to the surgery group only.

In sensitivity analyses, participants with a history of cancer before study inclusion and participants with a cancer event within the first three years after inclusion to the study will be excluded.

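### The single treatment-by-insulin term can describe how the surgery effect varies with insulin, but cannot attribute that variation to insulin rather than to a correlated modifier, above all sex

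*SAP*

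**What the plan says.** SAP section 4 (Statistical methods) gives the purpose of the test as "To formally test whether baseline insulin modifies the effect of bariatric surgery on cancer risk" and specifies that "an interaction term using the continuous insulin variable will be included in the Cox proportional hazards models". Tertiles of insulin are used only for description.

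The covariates come from the same section, which states that "analyses will be adjusted for major cancer risk factors defined by the American Cancer Society, age, sagittal diameter, alcohol consumption, and smoking". Insulin is added as a covariate: "serum insulin levels, which have previously been associated with cancer risk in sub-analyses in the SOS study, will be adjusted for". The purpose given for the adjustment is "To account for baseline differences between the surgery and control groups", which means balance between the groups, not separation of one effect modifier from another.

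The only other interaction with treatment concerns time: the proportional-hazards assumption is to be "evaluated by assessing the interaction between treatment and the logarithm of time". Sex is not named among the covariates; the separate handling of men and women is stated only for the BMI-change models. The sensitivity analyses remove people with earlier or early cancers and do not touch the interaction.

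Section 1 (Study objectives) recalls that the SOS study "reported an association between surgery-induced weight loss and lower cancer incidence in women, but not men". It also points to glycaemic markers as a suggested link between surgery and lower cancer risk, and it declares all the analyses post hoc and exploratory.

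**The concern.** Adjusting for a characteristic as a main effect removes its influence on the hazard, equally in both groups. It leaves untouched any influence of that characteristic on the surgery effect. If such a modifier is correlated with insulin and its own product with treatment is not in the model, the treatment-by-insulin term takes up part of its effect.

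The SAP itself supplies a candidate: sex, through the earlier result in section 1. Section 2.2 also sets different BMI thresholds for entry (34 in men, 38 in women), so body size at entry is tied to sex by design. Sagittal diameter and age are further characteristics that may plausibly be correlated with insulin, although the SAP reports no correlations.

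What is at stake is interpretation. Insulin is the only baseline characteristic whose modifying role is formally tested, and section 1 is interested in glycaemic markers as part of the mechanism. A positive single-term result would be read in that light, and no planned analysis shows whether it survives once sex or body size is allowed to modify the surgery effect too.

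**Working it through.** **Inputs.** From SAP section 2.1: 2007 surgery and 2040 control participants, 4047 in all. The SAP gives no event count, correlation, effect size or significance level for this test, so there is no planned figure to reproduce. Everything else below is assumed.

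**Step 1: what the single term estimates.** Let T be treatment, I insulin and M another characteristic, with I and M standardised and correlated at r. The planned model, reading adjustment as main effects, is

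log hazard = baseline + βT + γI + δM + θ(T×I).

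Suppose the surgery log hazard ratio (HR) is a + κM and does not depend on I once M is known. The average of M at a given insulin value is about rI, so the average surgery log HR at that value is about a + κrI. The term θ therefore estimates about κr, not zero. The main effect δM is the same in both groups and does not alter this.

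*Continuous modifier*, κ = −0.20 per SD (ratio of HRs exp(−0.20) = 0.82). Expected ratio per SD of insulin, exp(−0.20r):
- r = 0.2: exp(−0.04) = 0.961
- r = 0.35: exp(−0.07) = 0.932
- r = 0.5: exp(−0.10) = 0.905

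*Sex as modifier*, HR 0.60 in women and 1.00 in men, 71% women, insulin lower in women. The SD of the sex indicator is √(0.71 × 0.29) = 0.454, so κ = ln(0.60) × 0.454 = −0.232 per SD. Expected ratio per SD of insulin, exp(0.232r): 1.047, 1.085 and 1.123 at r = 0.2, 0.35 and 0.5.

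**Step 2: simulation with those inputs.** Cox models, 1000 replicates per cell, two-sided 5% Wald test, about 545 to 830 events, M always in the model as a main effect. Insulin has no modifying role independent of M. Ranges are over the two event counts.

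| True modifier | r | Ratio of HRs per SD insulin, single term | Rejection, single term | Rejection with T×M added |
|---|---|---|---|---|
| None | 0.2 to 0.5 | 0.995–1.003 | 3.4–6.1% | 4.0–6.3% |
| Continuous | 0.2 | 0.960–0.962 | 7.7–8.9% | 5.4–5.8% |
| Continuous | 0.35 | 0.931–0.934 | 12.9–17.7% | 4.3–5.9% |
| Continuous | 0.5 | 0.904 | 22.7–30.1% | 4.2–6.5% |
| Sex | 0.2 | 1.048–1.049 | 9.5–10.8% | 4.2–5.9% |
| Sex | 0.35 | 1.089–1.091 | 16.9–24.1% | 4.7–5.3% |
| Sex | 0.5 | 1.126–1.132 | 30.9–38.2% | 4.1–4.8% |

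The Monte Carlo standard error near 5% is √(0.05 × 0.95/1000) = 0.7 percentage points. The simulated ratios agree with Step 1. With T×M added, the insulin ratio in the modified scenarios returns to 0.997–1.003. The direction depends on the modifier: here the continuous one makes surgery look more effective at high insulin, and sex makes it look less effective.

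**Step 3: does the main effect protect?** No. With M left out of the model altogether, the rejection rate is 30.0% against 30.1% (continuous, r = 0.5, larger event count) and 38.3% against 38.2% (sex, same setting).

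**Step 4: a second set of assumptions.** 800 replicates, about 910 to 920 cancers, administrative censoring between 21.9 and 35.3 years (from the enrolment dates in section 2.1 to the end of 2022), other-cause censoring of 1.2% a year. Single-term rejection:
- Sagittal diameter changes the surgery log HR by 0.20 per SD: 14%, 31% and 44% at r = 0.3, 0.5 and 0.6.
- The same with 0.10 per SD: 8%, 11% and 14%.
- HR 0.65 in women and 1.0 in men, insulin 0.25, 0.5 or 0.8 SD higher in men: 7%, 11% and 17%.

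Adding treatment-by-sex, treatment-by-sagittal-diameter and treatment-by-age brings the rate to 4–6% throughout. The SD of the insulin interaction estimate rises by about 5% to 27%.

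**The case against.** The strongest objection is that these rejections are not false for the question as the plan words it. If M modifies the surgery effect and insulin tracks M, the surgery HR really does vary across insulin. Step 1 gives that gradient, and the single-term model recovers it. A marker that only stands in for another characteristic can still help to show who benefits. This stands. A reader might infer that the planned test has an inflated type I error and is invalid; as a test of heterogeneity along insulin it is not. The excess rejections count as errors only if the result is read as modification by insulin in its own right.

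Other tempting readings also fail:

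- *That the problem comes from the lack of randomisation.* The mechanism is the same in a randomised trial, and nothing in the calculation makes treatment depend on covariates.
- *That section 1 establishes sex as a modifier.* An association seen in one sex and not in the other is not an interaction estimate, and none is given. It makes sex a credible candidate, no more. For sagittal diameter and age the SAP offers no evidence of modification.
- *That a null result would hide a real insulin effect.* Offsetting modifiers could do this in principle, but it was not calculated.
- *That the SAP says covariates enter as main effects only.* This is inferred from its wording on adjustment and from the absence of other product terms. It is the natural reading, but not an explicit statement. If the reference to American Cancer Society risk factors were meant to cover sex as well, Step 3 shows that a main effect would not help.

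The plan is also exploratory throughout and ties no decision rule to this test. That limits the consequence, but it does not give the plan a way to tell the two explanations apart.

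**Conclusion.** The point holds as a limit on what the planned analysis can support. The single term is a valid description of how the surgery HR varies with baseline insulin. It cannot attribute that variation to insulin, and no other planned analysis can. Sex is the clearest gap, because the SAP's own background raises it while the covariate list and the interaction model leave it out.

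The size is uncertain. Under the assumed inputs, the chance that a nominal 5% test points to insulin when insulin has no independent role runs from about 7% to 44%. The upper end needs a correlation of 0.6 together with a change of 0.20 in the surgery log HR per SD; the weaker settings give 7% to 14%. None of the correlations, modifier strengths or event counts comes from the SAP, so these figures show the mechanism and its plausible range. They are not estimates for this study.

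**What to change.** Keep the planned treatment-by-insulin test as the descriptive result. Add to SAP section 4 a sensitivity model that also contains the sex main effect and treatment-by-sex, treatment-by-sagittal-diameter and treatment-by-age. Omit the sex terms for female-specific cancers. Report the insulin interaction, with its confidence interval, with and without the added terms.

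State the interpretation in advance: a single-term result is described as heterogeneity of the surgery effect along insulin, and it is attributed to insulin itself only with reference to the jointly adjusted estimate and its confidence interval. This should not become a rule that discards the single-term gradient when the joint estimate is imprecise.

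The cost is a short SAP edit and one further model per endpoint, with data already in hand. The jointly adjusted estimate is less precise (SD about 5% to 27% larger under the assumed inputs); the planned estimate is unaffected. The choice of three competing terms is a judgement. Smoking and alcohol are also in the covariate set and could be added at a further loss of precision.

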## 5. Version history

**Version 4, 2025-10-01 (current version):** Additional analyses included during a review process: more detailed analyses on time-varying risk; added analyses with restricted survival-time approach.

**Version 3, 2024-11-15:** Included analyses on cancer types (obesity-related cancers; female-specific cancers). Analyses on association between weight change and cancer risk in the surgery group added. Register-data was updated to include data until 31.12.2022. Analysis of case-fatality removed.

**Version 2, 2023-04-03:** Added analyses on cancer mortality, based on reviews of case sheets and autopsy reports. Sensitivity analyses added. Analyses on case-fatality included. More details on statistical methods added.

**Version 1, 2021-01-14:** First version focusing on time to total cancer incidence (fatal and non-fatal) in the surgery and control groups.
